# Obstructive Sleep Apnea and a Comprehensive Remotely Supervised Rehabilitation Program: Protocol for a Randomized Controlled Trial

**DOI:** 10.2196/47460

**Published:** 2023-09-18

**Keywords:** obstructive sleep apnea, telerehabilitation, telemonitoring, CPAP, apnea-hypopnea index, telehealth, telemedicine, sleep, respiratory, home based, rehabilitation, RCT, randomized controlled trial

## Abstract

**Background:**

Obstructive sleep apnea (OSA) is characterized by recurrent, intermittent partial or complete obstruction of the upper respiratory tract during sleep, which negatively affects the patient's daily quality of life (QoL). Middle-aged and older men who smoke and have obesity are most at risk. Even though the use of continuous positive airway pressure (CPAP) during sleep remains the gold standard treatment, various rehabilitation methods, such as exercise, respiratory therapy, myofunctional therapy, and nutritional lifestyle interventions, also appear to be effective. Moreover, it is increasingly recommended to use alternative or additional therapy options in combination with CPAP therapy.

**Objective:**

This study aims to evaluate if a comprehensive home-based, remotely supervised rehabilitation program (tele-RHB), in combination with standard therapy, can improve OSA severity by decreasing the apnea-hypopnea index (AHI); improve objective parameters of polysomnographic, spirometric, anthropometric, and body composition examinations; improve lipid profile, maximal mouth pressure, and functional capacity tests; and enhance the subjective perception of QoL, as well as daytime sleepiness in male participants with moderate to severe OSA. Our hypothesis is that a combination of the tele-RHB program and CPAP therapy will be more effective by improving OSA severity and the abovementioned parameters.

**Methods:**

This randomized controlled trial aims to recruit 50 male participants between the ages of 30 and 60 years with newly diagnosed moderate to severe OSA. Participants will be randomized 1:1, either to a 12-week tele-RHB program along with CPAP therapy or to CPAP therapy alone. After the completion of the intervention, the participants will be invited to complete a 1-year follow-up. The primary outcomes will be the polysomnographic value of AHI, Epworth Sleepiness Scale score, 36-Item Short Form Health Survey (SF-36) score, percentage of body fat, 6-minute walk test distance covered, as well as maximal inspiratory and expiratory mouth pressure values. Secondary outcomes will include polysomnographic values of oxygen desaturation index, supine AHI, total sleep time, average heart rate, mean oxygen saturation, and the percentage of time with oxygen saturation below 90%; anthropometric measurements of neck, waist, and hip circumference; BMI values; forced vital capacity; forced expiratory volume in 1 second; World Health Organization’s tool to measure QoL (WHOQOL-BREF) score; and lipid profile values.

**Results:**

Study recruitment began on October 25, 2021, and the estimated study completion date is December 2024. Analyses will be performed to examine whether the combination of the tele-RHB program and CPAP therapy will be more effective in the reduction of OSA severity and improvement of QoL, body composition and circumferences, exercise tolerance, lipid profile, as well as respiratory muscle and lung function, compared to CPAP therapy alone.

**Conclusions:**

The study will evaluate the effect of a comprehensive tele-RHB program on selected parameters mentioned above in male participants. The results of this intervention could help the further development of novel additional therapeutic home-based options for OSA.

**Trial Registration:**

ClinicalTrials.gov NCT04759456; https://clinicaltrials.gov/ct2/show/NCT04759456

**International Registered Report Identifier (IRRID):**

DERR1-10.2196/47460

## Introduction

### Background

Obstructive sleep apnea (OSA), the most common type of sleep-related breathing disorder [1], is characterized by recurrent, intermittent partial or complete collapse or obstruction of the upper respiratory tract during sleep [2]. Risk factors for its development include male gender, middle and older age, tobacco use, and obesity [3,4]. The high worldwide prevalence and increased risk of morbidity and mortality, especially due to cardiovascular diseases, make OSA a serious health-related global problem [5-7]. In addition, OSA can negatively affect the patient’s quality of daily life (QoL) [8]. For instance, excessive daytime sleepiness; impaired cognitive functions; work performance; ability to concentrate; or the occurrence of depression, headaches, snoring, and nocturnal urination; or disharmony in social interactions are particularly limiting [9,10]. The gold-standard treatment for OSA is continuous positive airway pressure (CPAP). The aim of CPAP therapy is to reduce the frequency of apneic and hypopneic pauses during sleep [11,12]. It is increasingly recommended to use alternative or additional therapy options in combination with CPAP [13]. These options include lifestyle and nutrition interventions, physical activity, pharmacotherapy, and behavioral therapy [13]. A recent meta-analysis has shown that a positive effect of exercise therapy, together with a reduction-diet intervention, leads to a significant reduction in the severity of OSA [14]. Based on several meta-analyses, the severity of the disease could be improved either by adjusting to a more nutritional lifestyle [14-16] or by implementing a physical intervention [17,18]. A significant reduction in the apnea-hypopnea index (AHI) was also achieved by training orofacial muscles with oropharyngeal exercises (ie, myofunctional therapy) [19]. According to Camacho et al [19], myofunctional therapy could represent an additional part of OSA therapy. Even the standard treatment representing CPAP therapy or mandibular advancement devices should also include exercise training [20]. A recent meta-analysis also showed a positive effect of respiratory therapy and respiratory muscle training elements in influencing OSA [21]. However, the authors stated that further research is needed to confirm the effect of additional therapeutic options already mentioned [12,15,17-19,21].

Aerobic and respiratory muscles training, oropharyngeal exercises, and regimen recommendations concerning lifestyle, nutrition, and behavior changes are individual components of the comprehensive home-based remotely supervised rehabilitation (tele-RHB) program conceived in this study. No recent literature has been found that deals with the effects of a similar and thus complex remotely supervised intervention. The absence of such an intervention in the context of OSA, as a possible therapeutic option for additional at-home training in combination with CPAP therapy, was the reason for conducting our research.

### Objective

This study protocol describes the first-ever randomized controlled trial to solely evaluate the effectiveness of the tele-RHB program among male adults with moderate to severe OSA. This study aims to assess whether completing a comprehensive telerehabilitation program and CPAP therapy positively affects the severity of OSA, QoL, body composition and circumferences, exercise tolerance, lipid profile, and respiratory muscle and lung function. Our hypothesis is that a combination of tele-RHB program and CPAP therapy will be more effective in the reduction of OSA severity and improvement of QoL, body composition, exercise tolerance, lipid profile, as well as respiratory muscle and lung function, compared to CPAP therapy alone.

## Methods

### Study Design

This study is a 2-arm parallel single-blind randomized controlled trial (registered on ClinicalTrials.gov: NCT04759456), with the per-protocol analysis investigating the effect of the tele-RHB program among 50 male patients with newly diagnosed OSA indicated to CPAP therapy. Patients were recruited from the Sleep Centre of the International Clinical Research Center of St Anne's University Hospital in Brno (FNUSA-ICRC). After providing informed consent, the patients will be randomized to the 12-week tele-RHB program along with CPAP therapy; 25 patients will be randomized to the intervention arm, and 25 will be in the control arm (CPAP therapy alone) in a 1:1 ratio, following the methods described below (Figure 1).

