### Exclusion Criteria

Participants are excluded if they have another type of OSA treatment, chronic corticosteroid therapy or long-term oxygen therapy; they are also excluded if they have at least one of the following health problems: central sleep apnea, chronic obstructive pulmonary disease III or IV, severe pulmonary hypertension, New York Heart Association III or IV, acute coronary syndrome, heart failure, ejection fraction <40%, electrocardiographic-documented heart arrhythmia, severe heart valve disease, cerebrovascular disease, psychiatric disease, and physical disability; in addition, they will be excluded if they do not cooperate during the intervention or do not follow the tele-RHB program and CPAP therapy protocol.

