### Recruitment, Enrollment, and Procedure

The patients who meet the inclusion criteria will be recruited from the Sleep Centre of the FNUSA-ICRC. The details of the study overview are shown in Table 1. On the first visit, patients will undergo polysomnography (PSG), blood sampling for lipid profile, and completion of the Epworth Sleepiness Scale (ESS) with a known score. Those who are found to have moderate to severe OSA will be contacted for further intervention alongside the standard CPAP therapy. These patients will be verbally informed and will receive an information leaflet about the ongoing study of the 12-week tele-RHB program. Then, they will complete anthropometric and spirometric examinations, measurements of maximal inspiratory mouth pressure (MIP) and maximal expiratory mouth pressure (MEP) as well as body composition, 6-minute walk test (6MWT), and QoL questionnaires in the Cardiovascular Rehabilitation Clinic at the University Hospital Brno (CRC-UHB). After that, during the interview with a physiotherapist, participants will receive detailed and comprehensive information regarding their possible participation in the study. Then, potential participants will be given at least 24 hours to decide before signing the informed consent.

On the second visit, patients who agreed to participate in the study will sign the informed consent form and will be then randomized 1:1 to the intervention or control group.

On the third visit, participants of both groups will undergo individual titration of CPAP therapy at the Sleep Centre of the FNUSA-ICRC. The intervention group will subsequently receive education about the tele-RHB program, along with theoretical and practical instruction on its individual components in the CRC-UHB. Participants of the intervention group will also receive a training brochure containing information needed for the tele-RHB program with remote supervision by a physiotherapist.

After the completion of the 12-week tele-RHB program, on the fourth visit, participants of both groups will undergo the same examinations and measurements as those conducted at the baseline, at the Sleep Centre of the FNUSA-ICRC and in the CRC-UHB.

After 1 year from the 12-week tele-RHB program’s completion, on the fifth visit, participants of both groups will undergo the same examinations and measurements as they did at the baseline in both health facilities.

**Table 1 table1:** An overview of the study flow.

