#### Intervention Group

Participants of the intervention group will undergo home-based 12-week tele-RHB program with regular teleconsultations via phone calls and emails at least 1-2 times a week with a physiotherapist. Teleconsultations will include telemonitoring and analysis of previously completed training sessions and the current course of the program; additionally, telecoaching for upcoming training sessions and motivation to continue the program will also be provided. Participants will also record the details of their completed training sessions during the intervention in a training diary and will regularly send it to the physiotherapist for evaluation. As previously stated, participants will receive a training brochure with a detailed description of the tele-RHB program and its components (Multimedia Appendix 1). Tele-RHB program will include nutrition, health-related lifestyle and behavior change recommendations, and a minimum of 5 times a week—each lasting 30 minutes—of moderate-intensity aerobic training; in addition, there will be 10 minutes of inspiratory and 10 minutes of expiratory muscle training with breathing devices (Threshold IMT and Threshold PEP) and 10 minutes of oropharyngeal exercise along with individually titrated CPAP therapy. After the completion of the 12-week tele-RHB program, participants should be motivated to continue performing this comprehensive rehabilitation program in home conditions during the 1-year follow-up, but without the regular remote supervision by a physiotherapist. This tele-RHB program was developed based on previous research or guideline recommendations for patients with OSA or cardiovascular diseases [6,29-36].

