#### Control Group

Participants of the control group will undergo individually titrated CPAP therapy alone, throughout 12 weeks.

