Our study intends to determine whether the completion of a tele-RHB program positively affects OSA in middle-aged and older men, and therefore, provide evidence for a possible recommendation of this tele-RHB program as an effective adjunctive treatment to CPAP therapy in male patients. The study will focus on the expected improvement in OSA severity, QoL, body composition, exercise tolerance, lipid profile, as well as respiratory muscles and lung function, resulting from the completed intervention.

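### Only a per-protocol analysis is named and non-adherence after randomisation leads to exclusion, by a test that differs between arms, so the comparison loses the protection of randomisation

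*Protocol article*

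**What the plan says.** Under Study Design, the article describes a two-arm randomised trial "with the per-protocol analysis investigating the effect of the tele-RHB program among 50 male patients". Neither the Statistical Analysis section nor any other part names an analysis of all randomised participants, even as a sensitivity analysis.

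The Exclusion Criteria list health conditions and then add that "they will be excluded if they do not cooperate during the intervention or do not follow the tele-RHB program and CPAP therapy protocol". Under Recruitment, Enrollment, and Procedure, men who agree to take part "will sign the informed consent form and will be then randomized 1:1 to the intervention or control group" at the second visit. CPAP titration and education follow at the third visit, and the 12-week programme comes after that.

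What has to be followed differs by arm. The Intervention Group section requires "a minimum of 5 times a week—each lasting 30 minutes—of moderate-intensity aerobic training", with inspiratory and expiratory muscle training, oropharyngeal exercise and CPAP. In contrast, "Participants of the control group will undergo individually titrated CPAP therapy alone, throughout 12 weeks".

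The Objective is "to solely evaluate the effectiveness of the tele-RHB program among male adults with moderate to severe OSA", with the hypothesis that the combination does better than CPAP alone. The Discussion hopes to "provide evidence for a possible recommendation of this tele-RHB program as an effective adjunctive treatment to CPAP therapy in male patients".

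**The concern.** An adherence condition written among the exclusion criteria looks like an eligibility rule. Because randomisation comes before titration, education and the programme, it can only operate as a rule for removing randomised men. The named analysis then compares those who remain.

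The test for remaining is not the same in the two arms. A man in the intervention arm can be removed for failing the exercise programme or CPAP, a control only for failing CPAP. Men who keep to a demanding home programme may well differ from those who do not in motivation, weight change and general health behaviour, all of which could affect AHI and the other primary outcomes. After such removal, a difference between arms can reflect who was kept rather than what was assigned. In a superiority trial this is not a conservative choice, and here no other analysis is named against which to check it.

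**Working it through.** **1. The plan's own figure.** The Sample Size section gives an AHI improvement of 8 with SD 10, 80% power and α = 0.05. Two-sided, n per arm = 2 × (1.96 + 0.84)² × 10² / 8² = 24.5, rounded up to 25. The stated 25 per arm is reproduced. By the t distribution, power at 25 per arm is 79.1%. The number calculated is also the number randomised ("25 patients will be randomized to the intervention arm, and 25 will be in the control arm (CPAP therapy alone) in a 1:1 ratio"), so nothing is set aside for exclusions.

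**2. When the exclusion acts.** Randomisation is at visit 2 and the programme starts after visit 3. Not following the programme cannot be observed before randomisation.

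**3. Size of the possible bias, on assumptions.** The documents give neither an expected exclusion rate nor an adherence threshold. Assume no true effect, SD 10 for AHI change, 25 randomised per arm, and a normally distributed adherence tendency that has correlation r with AHI improvement. The least adherent fraction p of each arm is removed. The mean adherence tendency of those kept is m(p) = φ(z_p)/(1 − p), where z_p is the p-quantile of the standard normal and φ its density:

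- m(10%) = 0.1755/0.9 = 0.195
- m(30%) = 0.3477/0.7 = 0.497
- m(40%) = 0.3863/0.6 = 0.644

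The spurious benefit is 10 × r × [m(intervention) − m(control)]:

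- 30% v 10%: 10 × 0.3 × 0.302 = 0.9; at r = 0.5, 1.5
- 40% v 10%: 10 × 0.3 × 0.449 = 1.3; at r = 0.5, 2.2
- 40% v 30%: at r = 0.5, 10 × 0.5 × 0.147 = 0.7
- equal rates: 0
- 30% v 40%: at r = 0.5, −0.7, that is, against the programme

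Simulation gives the type I error of the unpaired t test. The ranges below cover two ways of applying a rate: a cut-off on the adherence scale, or a whole number of men (30% of 25 is 7.5, so 7 or 8).

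| Excluded, intervention v control | r = 0.3: bias (events/h), type I error | r = 0.5: bias (events/h), type I error |
|---|---|---|
| 30% v 10% | 0.9 to 1.1, about 6% | 1.5 to 1.8, about 7% to 10% |
| 40% v 10% | 1.3 to 1.5, about 7% | 2.2 to 2.4, about 10% to 12% |
| 40% v 30% | 0.4 to 0.5, about 5% | 0.6 to 0.9, about 6% to 7% |
| 30% v 30% | about 0, about 5% | about 0, about 5% to 6% |
| 30% v 40% | sign reversed | 0.6 to 0.9 against the programme |

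Against the planned 8 events/h, 0.9 to 2.4 is 11% to 30%. In this model the bias comes from unequal exclusion, not from exclusion as such.

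**4. What analysing everyone costs in power.** If the 8 events/h already includes non-adherers, power stays at 79.1%. If it applies to adherers only and non-adherers gain nothing (an assumption), the difference becomes 8 × (1 − p). For 10%, 20% and 30% non-adherent this is 7.2, 6.4 and 5.6 events/h, with power at 25 per arm of 70%, 60% and 49%. At 30%, 52 per arm would be needed for 80% power. The per-protocol route loses power too: with 20% removed from both arms, 20 per arm remain and power for a difference of 8 is 69%.

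**The case against.** **A reader might infer that the bias must favour the programme.** The documents do not support that. The Discussion cites CPAP non-adherence of 30% to 80%, and the CPAP condition applies to both arms. A control exclusion rate of only 10% is therefore one corner of the range, and the one that produces the larger figures. The Discussion also says that teleconsultation, and the programme itself, may help CPAP adherence. If so, controls could fail the CPAP condition more often, which would offset or even reverse the imbalance. The correlations of 0.3 to 0.5 are assumptions as well. This objection stands: the direction is plausible, not established, and the size is unknown.

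**The trial may be asking about completers.** The Objective speaks of completing the programme, and the Discussion speaks of its completion. That is a fair reading of part of the text, so it would go too far to say that the protocol asks only about men who are offered the programme. But the same Objective claims effectiveness and superiority over CPAP alone. The completer reading does not rescue the comparison either: men who passed the programme's test are set against controls who never faced it, so the contrast is not a randomised one even for the effect of completing.

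**The analysis set might be settled elsewhere.** A condensed article may leave detail to a fuller plan. Here, though, the article itself states the analysis set and the exclusion, so this is not an omission.

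**Conclusion.** The point holds and should be corrected before analysis. From the text alone, the only named analysis is per-protocol, the exclusion acts after randomisation, and the adherence test is heavier in the intervention arm. Following the plan as written therefore gives up the protection of randomisation.

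The consequence for the estimate is less certain. Bias may go either way, more plausibly towards the programme because only that arm carries the extra hurdle. Under the stated assumptions it runs from about 0.9 to 2.4 events/h with a type I error of about 6% to 12% (30% to 40% v 10% excluded), through 0.6 to 0.9 events/h (40% v 30%, r = 0.5) and about zero at equal rates, to a reversed sign when more controls are removed. These figures show sensitivity; they do not predict the result.

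**What to change.** - Make the primary analysis all randomised participants in the arm to which they were assigned, regardless of adherence.
- Remove non-cooperation and non-adherence after randomisation from the exclusion criteria.
- Invite every randomised man to the post-intervention and one-year examinations (visits 4 and 5), including those already excluded where this is still possible.
- Keep per-protocol as a labelled supportive analysis, with adherence defined in advance for each arm and exclusions counted by arm.

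The visits are already scheduled, so the change is mainly an amendment and new analysis wording, but it has two real costs. The all-randomised effect may be smaller than 8 events/h, with power as low as about 49% if 8 applies to adherers only and 30% do not adhere and gain nothing. And since recruitment began in October 2021 and the article appeared in September 2023, week-12 data may be irrecoverable for men already excluded. Both should be reported, with the missing data counted by arm.

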**Figure 1 figure1:**
[figure not shown]
Flow diagram of the study protocol. CPAP: continuous positive airway pressure; tele-RHB: comprehensive home-based remotely supervised rehabilitation.

### Ethical Considerations

The study protocol follows the Declaration of Helsinki and received approval from the Ethics Committee of the University Hospital Brno in the Czech Republic (06-090920/EK). Participation in the study will be voluntary, without any compensation or remuneration, and participants will be allowed to withdraw from the study at any moment without providing a reason.

All participants will provide written informed consent. This informed consent form provides details about the purpose of the study, requirements for study participation, randomization process, personal data processing, storage and protection process, and contact information for research team staff. The original informed consent allows the secondary analysis of obtained data without additional consent.

All participants’ obtained data will be pseudonymized and deidentified; only an authorized person of the study research team will be able to identify the participants on the basis of personal data. The obtained data will be published anonymously, and no report or publication will contain any data that could lead to the participants’ identification.

